## Abstract

**Background:**

Protected engagement time (PET) is a concept of managing staff time on mental health inpatient wards with the aim of increasing staff and patient interaction. Despite apparent widespread use of PET, there remains a dearth of evidence as to how it is implemented and whether it carries benefits for staff or patients. This protocol describes a study which is being carried out on mental health wards caring for older adults (aged over 65) in England. The study shares a large proportion of the procedures, measures and study team membership of a recently completed investigation of the impact of PET in adult acute mental health wards. The study aims to identify prevalence and components of PET to construct a model for the intervention, in addition to testing the feasibility of the measures and procedures in preparation for a randomised trial.

**Methods/design:**

The study comprises four modules and uses a mixed methods approach. Module 1 involves mapping all inpatient wards in England which provide care for older adults, including those with dementia, ascertaining how many of these provide PET and in what way. Module 2 uses a prospective cohort method to compare five older adult mental health wards that use PET with five that do not across three National Health Service (NHS) Foundation Trust sites. The comparison comprises questionnaires, observation tools and routinely collected clinical service data and combines validated measures with questions developed specifically for the study. Module 3 entails an in-depth case study evaluation of three of the participating PET wards (one from each NHS Trust site) using semi-structured interviews with patients, carers and staff. Module 4 describes the development of a model and fidelity scale for PET using the information derived from the other modules with a working group of patients, carers and staff.

**Discussion:**

This is a feasibility study to test the application of the measures and methods in inpatient wards for older adults and develop a draft model for the intervention. The next stage will prospectively involve testing of the model and fidelity scale in randomised conditions to provide evidence for the effectiveness of PET as an intervention.

**Trial registration:**

ISRCTN31919196

## Background

The UK government has identified improving health and social care services for people with dementia as a national priority in a 5-year plan [1]. Over 700,000 people in the UK suffer from dementia, and this is projected to rise by 40 % by 2025 [2]. Two thirds of all UK hospital admissions of people over 65 and one quarter of all inpatients have dementia. As the level of cognitive impairment caused by dementia increases, so the way in which the person affected by dementia expresses their needs may change, with confusion and agitation as well as possible verbal and physical acts of aggression often presenting a challenge for carers. One factor frequently cited as contributing to agitation and other signs of distress in people affected by dementia, particularly within institutional care, is a lack of activity [3]. Behavioural and psychological difficulties are common in dementia and include confusion, agitation and possible aggression. Edvardsson and Nordvall [4] reported that people with dementia described boredom as part of their experience on a hospital ward. Pulsford [5] suggests that there is an absence of activities on wards for people with dementia as nurses may lack both time and confidence in their abilities to deliver them.

Protected engagement time (PET) is a relative newcomer among inpatient ward models intended to improve care delivery. It was first noted in mental health settings around 2004 [6] potentially arising from concerns in publications which reported that patients were bored, had little contact with staff and felt unsafe on acute wards [7, 8]. The Refocusing Model [9] contributed to the development of PET as an intervention through the subsequent decade and its use with older people on inpatient mental health wards has developed from this work.

The Refocusing Model had been implemented from 1999 in acute psychiatric wards in three National Health Service (NHS) trusts in England with reported benefits in terms of reduced staff sickness and absence, complaints, length of stay and use of formal observation. It involved increasing time for nurses to spend in one to one interaction with patients, an emphasis on nurses’ involvement in decision-making in their daily activities, regular use of clinical supervision and promotion of a calm environment. PET used some of these elements and placed the interpersonal relationship between staff and patients at the centre of ward practice by re-organising ward routines to increase staff and patient contact with minimal interruption.

Additionally, occupational therapists (OTs) have traditionally been seen as providers of activities for patients in mental health wards whilst the main staff group involved in PET has been nurses. This intervention may therefore provide an opportunity for task sharing between the professional groups and challenge existing professional boundaries. The intervention seems to have emerged from ward practice rather than from a well-defined theory or body of evidence and it has not been clearly defined and manualised. However, the Acute Care Collaborative report [10] provides the only source of guidance on implementing PET and identifies thatRegular times for PET are established: at least once a week and up to every day, for between one hour and half a day (between 3–4 hours in the morning or afternoon, not including night time).During PET the ward is closed to visitors and professionals from outside the ward. Nurses are involved in the implementation of PET; whilst other ward staff participation appears to vary.During PET ward staff do not make phone calls or administrative dutiesEngagement may involve one to one meetings, group work, games or activities, or meals eaten together.

The same report describes positive feedback from the managers of services using PET, suggesting that it helps to create a calmer ward atmosphere. PET for older adult inpatients is a potentially attractive initiative as it may provide a calm yet stimulating environment and underlying distress such as agitation and other needs of patients affected by dementia, and other diagnoses, can be met effectively. However, robust evidence as to whether the difficulties in wards for older adults can be resolved by this means is still lacking, and there are some potential difficulties arising from PET, for example, the temporary exclusion of visitors to the ward may exacerbate the attachment needs of patients, depending on how ward staff choose to implement PET.

This study should have the potential to provide preliminary evidence as to the current level of use of PET, its effectiveness and clarification of its key components. The majority of data collection for the study will be carried out in three NHS Trust sites in England and will include all professional groups providing clinical care for patients. The intention of PET is to improve the amount of high-quality contact between ward staff and patients, with a potential benefit of increasing safety on wards through reducing incidents of falls and aggression. A description of nurses in the UK context includes both registered nurses and health care assistants (HCAs). The term ‘ward staff’ refers to nurses predominantly but also to medical staff, psychologists and occupational therapists that may be ward-based to varying degrees.

PET may also reduce distress and agitation without the use of psychotropic medication [11] which can have a significant effect on morbidity and mortality in older people [12]. The UK NHS spends £128 million annually on prescriptions for tranquiliser, hypnotic and antidepressant medications for people with dementia compared to £62 million spent on the two most commonly prescribed medications (tamoxifen and anastrozole) for the treatment of cancer across all health care settings [13]. PET could potentially reduce the use of tranquilisers and contribute to optimal utilisation of existing human resources, thus reducing NHS costs.

If the results from this study are positive then the uptake of PET may be increased, in anticipation of a larger trial of PET. If PET does not emerge as having positive effects this will also be important, as it will indicate that other paths to non-pharmaceutical solutions must continue to be sought.

### Study aims

This study aims ascertain prevalence of PET in older adult wards in England and to identify specific characteristics which contribute to the intervention. It also aims to assess the feasibility of the evaluation measures and methods used in the clinical setting to inform a larger randomised trial of the intervention. As PET has already been widely adopted, there is also a need for preliminary evidence as to how it has been implemented and whether there is evidence of positive benefits. We will compare a sample of wards where this model is currently used with otherwise similar local wards where it is not. The main research questions are:How widespread is the use of PET in England on older adult mental health wards?Do patients on older adult wards with PET spend more time in contact with staff than on other similar wards without PET?Are there differences between patient experiences on wards with and without PET?Are there differences between staff experiences on wards with and without PET?Are there differences between rates of adverse incidents on wards with and without PET?Are there differences between prescribing of tranquilisers on wards with and without PET?How do patients, carers and ward staff experience PET, and what suggestions do they have about how to implement it?What are the main components of PET?

Our primary hypothesis is that levels of agitation will be decreased and quality of life will be improved for patients on wards where PET is in place.

## Methods/design

The study uses a mixture of quantitative and qualitative methods and has four distinct, but overlapping, stages or modules.Module 1: a service utilisation survey to determine prevalence of PET in older adult wards throughout EnglandModule 2: a prospective cohort comparison of patient and staff outcomes for a sample of five wards with and five without PETModule 3: a qualitative exploration of the views of patients, carers and staff in three wards with PETModule 4: development of a prospective model for the intervention.

A survey method has been selected to gather data on prevalence nationally as this is easiest to conduct within the study resources. We will use telephone interviews as they may yield a better response rate than on-line or postal returns and will allow the researchers to clarify any queries as they arise in the course of the interview [14]. The prospective cohort methodology used to compare outcomes for staff and patients in a smaller sample has been selected as it allows evaluation of routine current practice in two similar groups of wards. It benefits from being quick to implement and not requiring changes in practice or ward routine but has limitations in terms of potentially large confounding factors that are not controlled by randomisation [15]. Qualitative methods using individual semi-structured interviews provide the basis for the case study investigation of PET in three wards. The study uses this mixed methods approach as it appears most effective in evaluating complex interventions in health, such as PET [16, 17]. In developing the model for PET, we will combine frequency analysis from the service utilisation data with a concept mapping approach, which involves ranking components of the intervention in order of importance and relevance [18, 19].

The content of each module and their role in addressing the research questions are described in detail below.Module 1: Service utilisation survey to determine prevalence of PET in older adult wards throughout England

This module will address our first research question above on the prevalence of PET in older adult wards in England, which will be ascertained through telephone interviews with the ward managers or their nominated deputies. The interviews will use a questionnaire largely based on that used in the PET acute study, with modifications to relate more specifically to the older adult setting. Research question 8 on the components of PET will be addressed in this module through collection of data on whether PET is implemented and in what way, in addition to information on ward staffing, organisation and activities. The frequency and duration of PET will also be established. The study is supported by the Clinical Research Network (CRN) which is a UK public-funded body assisting in the delivery of large scale competitively funded research studies [20]. Input from CRN researchers will facilitate identification of wards and initial contact with managers to provide them with basic information about the study and invite them to participate in the survey. Their responses to the telephone questionnaire will be entered directly into an online survey system, Qualtrics [21], by the researcher. Responses from the survey will be summarised using descriptive statistics.2.Module 2: A prospective cohort comparison of patient and staff outcomes for a sample of five wards with and five without PET

We will employ a prospective cohort method to replicate that used in the preceding PET acute study, as this provides the most valid means of obtaining evidence for effectiveness of an already widely used intervention. This comparison comprises five sections: three sections will investigate the views and experiences of patients, carers and staff (research questions 3 and 4), the fourth will involve observational data on activities and interactions between staff and patients (research question 2), and the fifth will examine medication prescribing, incident rates (research questions 5 and 6) and staff sickness and turnover (research question 4). We will include 10 wards with approximately 15 patients per ward, and a low rate of turnover, giving an anticipated minimum number of 150 patients in total over the data collection periods.

### Comparison of the views and experiences of patients on wards with PET and those on wards without

#### Patient sample

All patients who have been in hospital for 14 days or more will be eligible to be included in the study, as the authors agreed that this time period would be adequate in which to have experienced life on the ward. There are two main types of in-patient service provision for older adults in England: wards specifically for those affected by dementia and other wards for all, irrespective of diagnosis. Both are represented in the study. We are unable to include patients who cannot communicate in English as the cost of translating documentation and hiring of interpreters is prohibitive within the study resources.

Capacity to consent to participating in the study is checked by the researchers with clinicians involved in the patient’s care and with access patient notes. If a patient is thought to have capacity, the researchers (all of whom are experienced registered clinicians) will check during contact with the patient themselves [22]. If they lack capacity a consultee (a family member or friend who knows them well and has visited at least twice during their hospital stay) can be asked to participate on behalf of the patient [23]. Patients with capacity and consultees of patients without capacity will be given a copy of the information sheet. Up to 1 week, but ideally no less than 24 h, later, the researcher will contact the patient or consultee to answer any queries they may have about the study and ask if they are happy to proceed (Fig. 1).

**Fig. 1 Fig1:**
[figure not shown]
Capacity and consent flow chart for patients

For the purpose of calculating an appropriate sample size, Dementia Health-Related Quality Of Life (DEMQoL) [24] was identified as the primary outcome measure for this study. The effect size from a previous study using this measure [25] was 0.53 and 0.43 (mean 0.48). If we were to observe a similar effect, we would require 70 participants per group. However, this would ignore the clustering (by ward). If the sample size is inflated for this assuming an intra-class correlation (ICC) of 0.01 and 24 individuals per ward then this increases to 86 per group. If the ICC is 0.05, then it is increased to 149 participants per group but we do not have any information about this parameter. However, as this is a feasibility study, one of the aims is to estimate the parameters required for a formal sample size calculation for a full trial.

We aim to include a minimum of three assessment wards (one at each site) with the remainder treatment/long stay wards. We will include a total of 10 wards: five with PET and five without. We estimated the average length of stay from this combined group as 3 months, based on recent figures from one of the participating sites. We anticipate recruiting 30 patients from the longer stay wards, and potentially 135 from the three assessment wards, over 9 months. This would give us 165 in one group, or a total of 330, which would give adequate power for the DEMQoL.

Completion of the questionnaires for this module will be with assistance from the researcher. Demographic information on age, gender and ethnicity will be collated, as well as whether the patient is detained under the mental health act. The Client Satisfaction Questionnaire (CSQ) [26] was selected for ease of comprehension and effectiveness, as was the EuroQoL measure (EQ5D) [27, 28]. This measure can have three or five levels in response to each question or dimension. We have chosen the latter, EQ5D-3L, for brevity. The Camden Content of Care Questionnaire (CCCQ) [29] enquires about areas of help received during the hospital stay. Additional questions have been added to the CCCQ to ascertain whether the patient felt they required each area of help and, if so, whether they received it.

Nurses will be asked to complete the Cohen Mansfield Agitation Inventory (CMAI) [3] for each patient participant. The researcher will check that the completing nurses know the patients well and have had the opportunity to observe their behaviour over a few days to enable accurate ratings. They will also complete a DEMQoL for staff and an EQ5D-3L proxy version to enable their perceptions of the patients’ quality of life to be compared to those of the patient or their carer.

Researchers will complete three symptom rating measures with assistance from staff who know the patient. These are the Mini Mental State Examination (MMSE) [30], selected due to established effectiveness in measuring cognitive impairment in this population, the Functional Assessment Staging (FAST) [31] to measure stages of deteriorating functioning, and the Clinical Global Impressions (CGI) [32] to compare present and past levels of functioning. The tools have been selected for brevity and ease of completion, to minimise time required from clinical staff (Table 1).

**Table 1 Tab1:** Patient related measures for module 2

Measure	Function	Completed by
Dementia quality of life (DEMQoL; patient or proxy version)	29 item measurement across 3 sub-scales of feelings, memory and behaviour, with a total score from 28 (good) to 112 (poor)	Patient or consultee
Client Satisfaction Questionnaire (CSQ)	8 item measurement of satisfaction with services and total score from 8 (worst) and 32 (best)	Patient
European quality of life—5 dimension (EQ-5D/EQ-5D proxy)	Measures perceived functioning in 5 areas—usual activities, mobility, anxiety/depression, pain/discomfort and self-care on three point scale for each	Patient or consultee
Camden content of care questionnaire (CCCQ)	Modified version of 21 item measure of help received whilst in hospital. Score from 0 (no help) to 147 (frequent)	Patient
DEMQoL (staff version)		Staff
Cohen Mansfield Agitation Inventory (CMAI)	Measures frequency on a scale of 1 (low) to 7 (high) of 29 behaviours with 4 sub-scales	Staff
Mini Mental State Examination (MMSE)	11 items testing five areas of cognitive function: orientation, registration, attention and calculation, recall, and language. Maximum score 30, with a score of 23 or lower indicative of cognitive impairment	Researcher
Functional Assessment Staging	Functional scale in 7 stages, from mild to severe incapacitation	Researcher
Clinical Global Impressions (CGI)	2 items a) Global severity, 7-point spectrum b) Global change, 9-point spectrum from improvement to deterioration	Researcher
Medication prescribing	Developed for the study to assess dosage and duration of prescribing for each medication	Researcher

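### The unqualified claim of adequate power for the DEMQoL is not delivered at the plan's own ICC of 0.05: 165 per group in five wards means 33 per ward, not the 24 used in the inflation

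*Protocol article*

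**What the plan says.** The sample size text is in the protocol article under Methods/design, Module 2, Patient sample, after Fig. 1. The DEMQoL "was identified as the primary outcome measure for this study". The effect size is 0.48, the mean of 0.53 and 0.43 from a previous study. Without clustering, "we would require 70 participants per group". With 24 patients per ward and an ICC of 0.01 this becomes 86. For the higher value the text says: "If the ICC is 0.05, then it is increased to 149 participants per group but we do not have any information about this parameter". It adds that, this being a feasibility study, "one of the aims is to estimate the parameters required for a formal sample size calculation for a full trial".

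The next paragraph fixes ten wards, five with PET and five without. It expects 30 patients from longer stay wards and potentially 135 from three assessment wards. That is 165 in one group or 330 overall, "which would give adequate power for the DEMQoL". The sentence names no ICC.

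Two other places bear on this. The introduction to Module 2 expects about 15 patients per ward and a minimum of 150 in total. The Background says of an unfavourable result: "If PET does not emerge as having positive effects this will also be important, as it will indicate that other paths to non-pharmaceutical solutions" must still be looked for.

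**The concern.** A reader sees 165 set against 86 and 149 and concludes that the design is covered at both ICC values. That comparison is valid only if the 165 patients sit in wards of about 24. With the number of wards fixed, more patients per group means larger wards, and the design effect rises with ward size. The 149 is therefore not the right yardstick for 165 patients in five wards.

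At stake is a power statement that readers will use to interpret the DEMQoL comparison. If it is too favourable, a non-significant difference will carry more weight than it should.

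**Working it through.** **Inputs.** Standardised difference d = 0.48; 70 per group unclustered; ICC 0.01 or 0.05; 24 per ward in the inflation; five wards per group; 165 per group (all from Patient sample). About 15 per ward and at least 150 in total (introduction to Module 2). Alpha and power are not stated. I take two-sided 5% and 80%, because these give the plan's 70, whereas 90% power would give 92.

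**Reproducing the plan.** The normal approximation gives 69 per group and the t-test version 69.1, rounded up to 70. The design effect is DE = 1 + (m − 1) × ICC. With m = 24:
- ICC 0.01: DE = 1.23; 70 × 1.23 = 86.1 (plan: 86).
- ICC 0.05: DE = 2.15; 69 × 2.15 = 148.35, rounded up to 149 (plan: 149); 70 × 2.15 = 150.5.

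The plan's three figures are therefore correct on their own terms.

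**Fitting them to five wards.**
- 149 / 24 = 6.2 wards per group, but the design has five.
- 5 × 24 = 120 per group, below 149.
- 165 / 5 = 33 per ward. At ICC 0.05, DE = 1 + 32 × 0.05 = 2.60.
- Effective size = 165 / 2.60 = 63.5, below 70. Put the other way, 70 × 2.60 = 182, above 165.

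**Power for d = 0.48**, using effective n = n / DE, by normal theory and by noncentral t on 10 − 2 = 8 degrees of freedom:

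| Per group | Wards | ICC | DE | Effective n | Normal | 8 df |
|---|---|---|---|---|---|---|
| 165 | 5 × 33 | 0.01 | 1.32 | 125.0 | 97% | 91% |
| 165 | 5 × 33 | 0.05 | 2.60 | 63.5 | 77% | 66% |
| 165 | 3 × 45 + 2 × 15 | 0.05 | – | 56–60 | 72–75% | 61–64% |
| 75 | 5 × 15 | 0.01 | 1.14 | 65.8 | 79% | 68% |
| 75 | 5 × 15 | 0.05 | 1.70 | 44.1 | 62% | 51% |

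The third row spreads the plan's 135 over three wards (45 each) and its 30 over two wards (15 each). The lower effective n uses the coefficient of variation of ward size; the higher one uses the sum of m / DE(m) over wards.

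Had the 2.15 design effect applied to 165, the effective size would be 165 / 2.15 = 76.7 and power about 84% by normal theory. Carrying over the wrong ward size therefore accounts for a fall from 84% to 77%. Counting wards rather than patients in the degrees of freedom accounts for the further fall to 66%.

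**Where the claim stops holding.** By normal theory, 165 in five wards keeps 80% power up to an ICC of (165/69 − 1) / 32 = 0.043.

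**Number needed in five wards at ICC 0.05.** n = n0(1 − ICC) / (1 − n0 × ICC / 5). With n0 = 70 this is 66.5 / 0.30 = 222 per group by normal theory (203 with the unrounded n0 of 68.13). On 8 degrees of freedom 222 gives only about 70% power, and about 765 per group would be needed for 80%.

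**Precision at ICC 0.05.** The 95% interval half-width on 8 df is 2.306 × √(2 × 2.60 / 165) = 0.41 SD at 165 per group, and 2.306 × √(2 × 1.70 / 75) = 0.49 SD at 75 per group.

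**The case against.** The best defence is that the plan admits it knows nothing about the ICC, offers 0.01 and 0.05 as illustrations, and does not tie its power statement to 0.05. At 0.01 the statement is right for 165 per group. By the plan's own kind of calculation the shortfall at 0.05 is about 3 points (77% against 80%). The larger shortfall depends on 8 degrees of freedom. The article commits only to regression adjusted for clustering by service and may properly leave small-sample corrections to an analysis plan. This is also a feasibility cohort, with a randomised trial to follow.

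Much of this stands. The absence of a degrees-of-freedom statement is not an error, and the problem is confined to the upper ICC value for 165 per group. But the power statement carries no qualification, it follows directly after the 149, and it fails at one of the only two ICC values the plan gives. Feasibility status would be a good reason to make no power claim; it does not make the one given correct.

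Three stronger readings are tempting and are not supported:
- *A null result would be likely even if the effect were real.* At 165 per group in equal wards and ICC 0.05 the chance is 23–34%; at 75 per group it reaches about 49%. No scenario in the table makes it more likely than not.
- *The plan will act on a null result.* The Background sentence is a general remark, not a decision rule. Elsewhere the article promises only preliminary evidence and acknowledges confounding.
- *A poor ICC estimate will mis-size the next trial.* The plan says only that it aims to estimate such parameters; nothing says that a bare point estimate will be carried forward.

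**Conclusion.** The point holds, limited to this: the power statement is wrong as written at ICC 0.05, because the inflation assumes wards of 24 while 165 patients in five wards makes wards of 33. The shortfall from 80% is modest by normal theory and about 14 points on between-ward degrees of freedom, and somewhat larger with unequal wards.

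No single actual ward size can be read from the article: 24 is assumed, 33 is implied and 15 is stated. At 15 per ward the design effect is smaller than the plan's, and power is low because only 75 per group are available. The 165 is itself in doubt. Study limitations reports that assessment wards closed at two sites and that the remaining one could not be included, and assessment wards were to supply 135 of the 165.

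The result rests on two-sided 5% and 80% (inferred), d = 0.48, a service in the clustering adjustment meaning a ward, and no gain from covariate adjustment, as in the plan's own calculation. Over the plan's two source effect sizes, power for 165 in five equal wards at ICC 0.05 runs from 68% / 57% (d = 0.43) to 85% / 74% (d = 0.53), normal theory / 8 df. At the upper effect size normal theory would therefore clear 80%, while the calculation on 8 df would not.

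**What to change.** 1. Recompute with five wards per group and m = n / 5, state alpha and target power, and reconcile the figures of 24, 33 and 15 per ward.
2. Replace the adequate-power statement with power at both ICC values for the sample now thought achievable, on between-ward degrees of freedom. For example: *With five wards per group, power to detect a standardised difference of 0.48 (two-sided 5%, 8 degrees of freedom) is about 91% at an ICC of 0.01 and 66% at 0.05 with 33 patients per ward, and 68% and 51% with 15 per ward.*
3. Qualify the Background sentence: a non-significant difference will be read through its confidence interval and not taken by itself as evidence that PET lacks benefit.
4. Report the ICC with its confidence interval. An estimate of 0.05 from ten wards has a 95% interval of about 0 to 0.24 (24 per ward) or 0 to 0.27 (15 per ward), which covers both planning values.

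The cost is a recalculation and some rewording, with no change to design or data collection. The downside is that the stated power becomes less favourable.
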